## Abstract

**Background:**

Gambling disorders affect about one percent of adults. Effective treatments are available but only a small proportion of affected individuals will choose to attend formal treatment. As a result, self-directed treatments have also been developed and found effective. Self-directed treatments provide individuals with information and support to initiate a recovery program without attending formal treatment. In previous research we developed an telephone-based intervention package that helps people to be motivated to tackle their gambling problem and to use basic behavioral and cognitive change strategies. The present study will investigate the efficacy of this self-directed intervention offered as a free online resource. The Internet is an excellent modality in which to offer self-directed treatment for gambling problems. The Internet is increasingly accessible to members of the public and is frequently used to access health-related information. Online gambling sites are also becoming more popular gambling platforms.

**Method/Design:**

A randomized clinical trial (N=180) will be conducted in which individuals with gambling problems who are not interested in attending formal treatment are randomly assigned to have access to an online self-directed intervention or to a comparison condition. The comparison condition will be an alternative website that offers a self-assessment of gambling involvement and gambling-related problems. The participant’s use of the resources and their gambling involvement (days of gambling, dollars loss) and their gambling problems will be tracked for a twelve month follow-up period.

**Discussion:**

The results of this research will be important for informing policy-makers who are developing treatment systems.

**Trial registration:**

ISRCTN06220098

## Background

### Significance

Gambling disorders are broadly defined as persistent and recurrent gambling that disrupts personal, family or vocational functioning [1]. Prevalence rates vary among jurisdictions according to availability and accessibility of gambling as well as definitional, measurement and other research design factors [2,3]. In Canada, all provinces have conducted one or more prevalence surveys and rates of problem gambling range from 0.7 to 1.4% of adults [4]. The personal, social, and economic costs of gambling disorders are large – including impairment or loss of relationships, stress-related medical problems, elevated risk of suicide, criminal offences and financial difficulties [3]. In addition, rates of comorbid mental health disorders such as mood, anxiety, attention deficit and substance use disorders are higher than expected [5,6].

Development and provision of effective treatment for gambling disorders is imperative. However, only about one in ten gamblers with a lifetime diagnosis of gambling disorder will ever seek treatment [7,8]. Many of these problem gamblers are unwilling to access treatment, often because of stigma, embarrassment or a desire to handle their problems on their own [9-12]. These problem gamblers, nonetheless, can be helped. Research has demonstrated the effectiveness of self-directed interventions for gambling problems [13-15]. This area deserves more attention because it addresses a cost-effective means of helping problem gamblers without requiring them to come to treatment. The aim of self-directed interventions is to help problem gamblers where they are, thus circumventing many of the barriers associated with traditional treatment.

#### Treatment outcome in disordered gambling

Outcome research for problem gambling treatment is limited but independent groups of investigators have begun to establish an evidence base in two related areas: cognitive-behavioral models [16-21] and brief self-directed treatments [22]. Brief treatments involve provision of self-directed written materials or limited contact with clients. For individuals not willing to seek formal treatment, brief interventions may be an attractive and effective, non-threatening alternative [23]. In two separate randomized clinical trials (N= 102, N = 314), we recruited individuals suffering gambling problems who wanted self-directed treatment but were not willing to attend formal treatment. Both trials supported the efficacy of a cognitive-behavioural self-help workbook sent via mail combined with a motivational telephone intervention [13-15]. The workbook was developed based upon earlier qualitative research on the process of recovery from pathological gambling [24,25]. It was designed to be brief, easy to read and to include practical change strategies [25]. It has been translated from English into a number of languages (French, Japanese, Portuguese, German, Swedish, and Norwegian) and is disseminated in a number of jurisdictions (e.g., Iowa, Oregon, Alberta). In the Hodgins et al. (2009) trial, participants at follow-up specifically identified using the workbook’s cognitive and behavioral strategies and viewed them as important in their recovery. A logical extension of this type of treatment is the use of the Internet as a platform for providing this type of self-directed treatment. Three factors support this direction: Internet access is widespread, the Internet is used to provide health treatment in a variety of areas and Internet-based gambling continues to grow.

#### The internet as a treatment platform

The use of the Internet as a platform has begun to be exploited in areas other than problem gambling. In the larger area of eHealth interventions, Portnoy and colleagues [26] reviewed 75 randomized controlled trials of different health behaviours and found general support for computer-based interventions. Despite the promise of the Internet, there remains limited research done in this area in regard to disordered gambling [23]. In Sweden, a randomized trial investigated the efficacy of a therapist-assisted web-based cognitive-behavioral program [27]. Compared with pathological gamblers on a waitlist, participants receiving the intervention had better gambling outcomes at three months. These gains were maintained over a 36 month follow-up interval. Cooper [28] and Wood [29,30] conducted qualitative studies investigating the use of online support groups among gamblers.

Our research team is also undertaking a randomized controlled trial of a brief personalized feedback intervention for problem gamblers (CYG; http://www.CheckYourGambling.net). In the CYG, the participant completes a brief assessment and then receives a personalized feedback report. Our pilot data (N = 61) indicated a decrease in gambling expenditures among individuals who volunteered to use the Internet self-assessment program [31], although our larger trial indicated that this effect is modest [32].

Such personalized feedback is often regarded as the first step in a self-directed brief intervention. However, there have been no reports of the development and evaluation of full Internet-based interventions that incorporate the full range of cognitive behavioural exercises that have been successful in paper-based self-directed formats. Problem gamblers have certainly indicated an interest in Internet-based services, with half of possible/probable pathological gamblers voicing an interest in a recent Ontario general population survey (N = 8467) [33]. The goal of this proposed research is to establish whether self-directed materials placed in an online context can provide a new tool to help problem gamblers deal with their concerns.

#### Access to the internet is crucial

The growing availability of the Internet makes it an ideal vehicle to help improve the accessibility of services for problem gamblers. Internet use has become widespread and is increasing. In 2011, 82% of Canadians had access to the Internet [34] and the majority of Internet users has accessed a health website [35]. Internet users include individuals with gambling disorders. A general population survey found that 73% of problem gamblers had home access to the Internet in Ontario in 2007 [36]. As our history of radio, TV and VCR ownership demonstrates, any remaining disparities in current use of the Internet across groups will likely reduce to the point that access is close to universal.

#### The growth of internet gambling

The first Internet gambling sites opened in 1995 and in 2011, there was an estimated 2400 sites operated by 650 different companies [37]. Estimates of participation rates in Canada range from 2.1% to 3.5% of adults [38], which are surprisingly high given that these companies are essentially operating illegally. Recently some provincial governments in Canada are beginning to offer legalized online gambling which will increase participation.

### Potential moderators and mediators of brief Internet interventions

How do brief interventions work and for whom? There has been little research into potential moderators and mediators of brief treatments in gambling disorders. In terms of moderators, exploratory analyses of our recent self-directed treatment for gambling problems (Hodgins et al. 2009) uncovered two factors that reliably predicted outcome- previous gambling or mental health treatment experience and self-efficacy. Participants who had no previous treatment and those that rated themselves as more likely to be successful had better outcomes regardless of the level of gambling problem severity. It is possible that these individuals are “natural” self-changers or, alternatively, that treatment-seeking is an indicator of one dimension of problem severity. Self-efficacy is often identified as a predictor of outcome from substance addictions [39,40] and may predict better success with self-help methods [41]. Self-efficacy can also act as a mediator of outcome. In our recent trial we found that improvement in self-efficacy as well as baseline self-efficacy correlated with improvement in gambling involvement [15]. In the smoking area, a study that compared an Internet-based cognitive-behavioural intervention to an information only control similarly found that self-efficacy was a significant mediator of cessation [42]. In the present study, we hypothesize that self-efficacy will both moderate and mediate outcome.

The Danaher et al. (2008) smoking trial identified program involvement as a second mediator. Participants who used program features more often, and completed more exercises, had better outcomes. A second Internet smoking cessation trial also found that program involvement mediated change [43]. Similarly, we hypothesize that degree of program involvement in the Self-Change Tools (SCT) intervention will mediate its increased `1`1`impact on reducing gambling behaviour compared with the control.

## Methods/Design

The proposed research will evaluate a full Internet-based self-directed intervention for problem gamblers using a single blind, randomized controlled trial comparing participants who are provided access to the SCTs as compared to those who are only provided the CYG personalized feedback screener (the control condition). There is one primary hypothesis and four secondary hypotheses:

Hypothesis 1**:** Respondents will display significant reductions in their gambling behaviour in the twelve months after being provided access to the online SCTs as compared to participants only provided with the normative feedback control intervention (CYG).

In addition, two potential moderators and two potential mediators of the impact of the full intervention, program involvement and perceived self-efficacy, will be tested as secondary hypotheses:

**Hypothesis 2:** Respondents with greater baseline self-efficacy will display significant reductions in their gambling behaviour in the twelve months after being provided access to the online SCTs or the CYG compared to participants with lower baseline self-efficacy.

**Hypothesis 3:** Respondents who have never accessed gambling or mental health treatment will display significant reductions in their gambling behaviour in the twelve months after being provided access to the online SCTs or the CYG compared to participants with previous treatment involvement.

**Hypothesis 4:** Respondents in the SCTs intervention condition who have more involvement with the SCTs intervention between baseline and three-month follow-up will demonstrate more improvement in gambling outcomes at six- and twelve-month follow-up, compared to respondents who have less involvement with the SCTs intervention.

**Hypothesis 5:** Respondents in the SCTs intervention condition will display significant increases in their perceived self-efficacy to deal with their gambling concerns in the three months after being provided access to the online SCTs as compared to participants in the control condition. Participants with greater improvement in self-efficacy will show greater improvement in gambling behaviour.

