### Process measures

We will have access to a complete record of the amount and type of use participants make of the SCTs (and the CYG). Following methods used by Danaher (2008) and Strecher (2008), we will operationalize degree of involvement with SCTs by recording the number of times the participant accesses the site as well as the number of tools the participant uses (as assessed by page views, form completions, etc.) and length of involvement with the site (e.g. use of the site over time). This information will be used to test the mediation hypothesis that degree of involvement is related to success at overcoming gambling problems.

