### Analyses plan

Primary analyses for Hypothesis 1, comparing outcomes for the two groups, will be based on the appropriate random effects model to properly account for the longitudinal nature of this data. Condition (2) and Time (0,3,6,12) will be modeled as fixed factors while the participants will be modeled as random factors. Separate analyses will be conducted for each primary and secondary outcome variable. This same analytic approach will be used for Hypothesis 2 and 3, examining moderators. Baseline self-efficacy, past use of treatment, and baseline NODS scores will be included as additional factors. For Hypothesis 3 and 4, the mediation hypotheses, the procedures recommended by Preacher and Hayes [58] will be conducted using a series of random effect models. Missing data should not be a major issue but techniques for these matters may be used depending on the nature, location and type of missingness.

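### Hypothesis 4 is labelled mediation, but as worded it compares heavier with lighter users inside the SCT arm, which cannot by itself show mediation

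*Protocol article*

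**What the plan says.** The protocol article describes the role of program involvement in five places.

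- **Background, potential moderators and mediators.** The authors expect that "degree of program involvement in the Self-Change Tools (SCT) intervention will mediate its increased" impact on gambling relative to the control. This is a between-arm claim.
- **Methods/Design, introduction to the secondary hypotheses.** It announces "two potential moderators and two potential mediators of the impact of the full intervention, program involvement and perceived self-efficacy".
- **Methods/Design, Hypothesis 4.** The people studied are "Respondents in the SCTs intervention condition who have more involvement with the SCTs intervention between baseline and three-month follow-up". Their outcome at six and twelve months is judged "compared to respondents who have less involvement with the SCTs intervention". Both groups are in the SCT arm.
- **Process measures.** Involvement is measured by number of visits, number of tools used and length of use, and "This information will be used to test the mediation hypothesis that degree of involvement is related to success at overcoming gambling problems". The same section says there will be a "complete record of the amount and type of use participants make of the SCTs (and the CYG"), so use of the control site, Check Your Gambling (CYG), is logged too.
- **Analyses plan.** "For Hypothesis 3 and 4, the mediation hypotheses, the procedures recommended by Preacher and Hayes [58] will be conducted" with a series of random effects models. No analysis set and no covariates are given for Hypothesis 4.

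The numbering in the last sentence is off: Hypothesis 3 is a moderator hypothesis, and by the list in Methods/Design the mediator hypotheses are 4 and 5. Hypothesis 4 carries the mediation label under either numbering.

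**The concern.** A mediation claim about a treatment says that assignment changes the mediator and that the change in the mediator changes the outcome. Hypothesis 4 contains no contrast in assignment. It sorts participants of one arm by how much they used the site.

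That sorting is done by the participants. The Self-change Tools section describes a menu from which they pick what suits them. The background reports that baseline self-efficacy went with improvement in an earlier trial and raises the possibility that some participants are natural self-changers. If such people also use the site more, which is plausible but not shown in the article, heavier users would do better even if use did nothing.

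The stake is the conclusion drawn. Under a mediation label, a positive Hypothesis 4 would be read as evidence that engagement with the tools produces the benefit. The Discussion addresses the results to policy-makers and service administrators, who could act on that reading.

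**Working it through.** **1. The plan's own figure.** The sample-size section gives 180 randomised, 15% attrition and about 153 followed: 180 × 0.85 = 153. Taking the stated medium effect as a standardised difference of 0.5 (an assumption, since no SD is given), α = .025 two-sided, power .80 and change scores with correlation .5 (variance factor 2(1 − .5) = 1):

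n per arm = 2 × (2.241 + 0.842)² / 0.5² ≈ 76.04, rounded up to 77; total 154; 154 / 0.85 = 181.2, rounded up to 182.

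This agrees with 153 and 180 to within about 1%. The calculation is for the randomised comparison. No figure is stated for Hypothesis 4, which rests on one arm: 153 / 2 = 76.5, about 76 with equal allocation (assumed).

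**2. What the comparison can estimate.** Write condition → use as path *a*, and use → outcome given condition as path *b*. The indirect effect in a linear model is *a* × *b*.

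- Within the SCT arm, condition does not vary, so *a* cannot be estimated. Only a slope of outcome on use is available.
- In a two-arm model with SCT use set to zero in controls, *a* is mean SCT use minus zero, and *b* comes from the same within-SCT slope, because controls have no variation in SCT use.

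So the Hypothesis 4 slope can be one ingredient of a mediation analysis, but it is not one by itself. In either setting it has a causal meaning only if use and outcome share no unmeasured cause.

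Hypothesis 5 shows the difference. It first states an SCT-versus-control contrast on self-efficacy and then links self-efficacy change to outcome. Hypothesis 4 has only the second part.

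**3. How far a common cause could carry the test.** Suppose use has no effect, and a baseline trait correlates *c* with use and *c* with improvement. The induced correlation is r = c². With n = 76, √(n − 3) = √73 = 8.544, and m = 8.544 × atanh(r). The rejection rate at two-sided .05 is Φ(m − 1.96) + Φ(−m − 1.96).

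| c (assumed) | r = c² | m | Rejection, formula | Rejection, 20,000 simulated trials |
|---|---|---|---|---|
| .2 | .04 | 0.342 | 6.4% | 6.4% |
| .3 | .09 | 0.771 | 12.0% | 12.0% |
| .4 | .16 | 1.379 | 28.1% | 28.3% |
| .5 | .25 | 2.182 | 58.8% | 59.4% |
| .6 | .36 | 3.220 | 89.6% | 90.1% |

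At α = .025, if the two-outcome correction were applied here (the article does not say), c = .4 and .5 give about 19% and 48%.

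For scale, 80% power on 76 people at two-sided .05 needs r = tanh((1.960 + 0.842) / 8.544) ≈ .32.

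**The case against.** Several stronger statements are tempting, and the article does not support them.

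- **That an indirect effect through SCT use does not exist.** A reader might infer this because controls have no SCT use. It does not follow. Condition moves use from zero to some level, and the effect of use at its actual level against no use is definable in a two-arm model, provided some SCT participants use little or nothing. The recruitment section, which recalls 30% never accessing the site in an alcohol trial, shows that the authors expect non-access to be possible. What is in doubt is the no-confounding assumption.
- **That the plan prescribes a one-arm, unadjusted model.** The analysis plan states neither. The restriction to one arm comes from the wording of Hypothesis 4. A condensed article may leave covariates to the full plan, and silence is not a decision against adjustment. The hypothesis also speaks of improvement and Time includes month 0, so the baseline outcome may already enter the model.
- **That reverse causation is uncontrolled.** Use is measured to three months and outcome at six and twelve. This limits the problem, although use by month three may partly reflect gambling change by then, and time order does not remove confounding.

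It is also fair to say that Hypothesis 4 is secondary, and that the Discussion describes analysis of use and outcome as correlational and meant to generate hypotheses. That remark concerns individual program components. It neither names Hypothesis 4 nor withdraws the mediation label used elsewhere.

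What stands is the mismatch between the hypothesis as worded and the claim attached to it. Label, population and method are all stated, so this is not detail deferred to another document.

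**Conclusion.** The point holds in limited form. As worded, Hypothesis 4 yields an association between self-chosen use and later outcome within the SCT arm. It cannot by itself support the statement that involvement mediates the SCT advantage over control.

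That conclusion follows from the text and does not depend on any numerical assumption. The 6% to 90% range is illustrative. It rests on assumed correlations, equal arms, the three-month follow-up number (fewer may be reached at six and twelve months) and a simple correlation test in place of the random effects model. At .2 to .3 the excess over 5% is modest (6% to 12%); from .4 upwards it is large.

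**What to change.** - **Restate Hypothesis 4** as an exploratory within-arm association of use to month three with outcome at six and twelve months, and drop the mediation claim for it.
- **Adjust for baseline** gambling days, NODS, GASS self-efficacy, treatment goal and treatment history. All are in the baseline assessment.
- **Give any result adjusted for three-month gambling only as a sensitivity analysis.** That variable may lie on the path from early use to later outcome, and adjusting for it could remove part of the effect sought.
- **If mediation is kept,** fit a two-arm model with condition as the exposure, state the assumption of no unmeasured use–outcome confounding, and add a sensitivity analysis for it. Visits or duration are logged on both sites but are not like exposures: CYG is a brief assessment with a feedback report, SCT a set of tools with continuing access.
- **Align the wording** in the background, the secondary hypotheses, the process measures and the analysis plan, and correct the numbering of the mediation hypotheses.

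The cost is wording and a few covariates, with no new data. The claim becomes weaker, and confounding by motivation would remain in part, because the baseline assessment lists no dedicated motivation scale.

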### Ethics approval

The research methods to be used in this study have been approved by the University of Calgary Conjoint Faculties Research Ethics Board (certificate 7279).

